#### Assignment of intervention

##### Allocation

At the end of Visit 2- subjects will be randomized at a ratio of 1:1:1 to each study group and stratified based on gender. Randomization will be conducted by a randomization software (computer generated random numbers) [34]. A third party who is not aware of research protocol will allocate patients into the study groups a priori to first recruitment using the randomization software and will create and keep the allocation list. Once recruitment for a particular baseline day and all baseline measurements are finished, a mediator in the IEMH (secretary) will contact the third party to reveal the allocations of the participants recruited and examined so far (allocation concealment).

##### Blinding

As mentioned we will use allocation concealment, such that at baseline all outcome assessors will be blinded to allocation. At follow up outcome assessors that will be blinded to the participants allocation will include: laboratory technicians (performing blood analysis); research assistant (AL) (in charge of nutritional analysis and the Med-diet questionnaire); ophthalmologist (for eye examination); endocrinologist (YM) (analyzing the 24–hour ambulatory blood pressure monitoring [ABPM]); another researcher (AD) (analyzing the quality of life questionnaires). The study physician (RE), nutritionist (AB), physiologist (OK) and physical instructor (AR) will not be blinded due to their role of instructing the patients on the intervention as well as collecting the following outcomes: body composition (automatic analysis but measured by AR); food intake and RMR (AB) and physical performance tests (OK).

### Intervention

#### Circuit resistance training (CRT)

Traditionally, the recommendations for physical activity in older adults (given by the ACSM and AHA) include 150 min of moderate intensity aerobic exercise/week and at least two resistance training exercise sessions (~ 60–90 min/session) /week [35]. As resistance training is considered to be the most appropriate form of intervention to decelerate muscle mass and strength loss [35] and keeping in mind the low adherence to the PA recommendations [17] we chose to focus on resistance exercise in the form of CRT. In this study subjects will be allocated to CRT which consists of 10 resistance exercises for different body parts (=1 circuit) repeated 12–15 times, using modest weights (approximately 40–60% of one repetition maximum, RM). Each exercise is expected to be completed within 30–40 s. The participant will move quickly (within 15–30 s) from one exercise to the next. The circuit will be repeated up to three times depending on the week of intervention. Thus, it will take about 30 min to complete an exercise session [22, 36]. Participants are expected to perform three full sessions per week on non-consecutive days. A summary of articles on CRT in older adults compiled in our meta-analysis are provided in ref. [22]. Also, for a detailed training program please see online Additional file 1.

#### “Vegeterranean” diet (V-med diet)

Briefly, the Med-diet is rich in olive oil, legumes, fish, chicken, nuts, milk products, fruits & vegetable. The modified V-Med diet in the study will be considered as ad-libitum (using fat sources) aimed for a minimum of 1 g/kg/day of protein, limiting carbohydrates: 3 servings for men and 2 servings for women per main meal and 1 serving per intermediate meal for both genders (medium/low glycemic index carbohydrates will be recommended). Subjects will be encouraged to consume ≥25 g of dietary fibers [37]. Subjects will be asked to avoid red meat and poultry completely and the consumption of dairy and eggs products will be limited to 2 servings per day. Three servings of fish should be consumed during the week. Legumes will comprise the source of the residual protein consumption, by the study’s team recommendations. The target legume consumption will be 0.75–1.5 cup per day (1–2 servings per day) of cooked beans, chickpeas or lentils and/or using pulses-based flour or pulses-based bread. Other sources for fibers will be recommended by consumption of whole grain carbohydrate foods (preferably millet, groats, bulgur, red-rice or “pseudo grains” like quinoa, buckwheat). Participants will be provided with a checklist of 15-g carbohydrate portions and of 10-g protein portions of recommended foods and the quantities they were expected to consume daily (as previously shown in [38]).

#### Empagliflozin (SGLT-2 inhibitor)

Subjects allocated to empagliflozin will be asked to add empagliflozin 10 mg, preferably in the morning, to their medication regimen. Subjects will be monitored for adverse events including hypoglycemic events during all study visits.

#### Measures of compliance/adherence

Compliance would be monitored in all three arms. Subject’s adherence to the exercise regimen will be assessed based on subject reporting and documentation in a dedicated booklet. Good compliance/adherence would be considered as performing ≥2/3 of original workout plan. Adherence to the V-Med diet will be based on a questionnaire scoring the diet implementation [39]. A score < 9 would be considered as low adherence, and ≥ 9 as high adherence. Adherence to the diet will also be assessed from 3-day food records or at least from 24 h recall report at the weeks 10 and 20 (visits 6, 9, respectively). For the drug arm, a recall of unused tablets would be performed after 10 weeks and at the end of the study. Consumption of less than 80% of study medication would be considered poor adherence to therapy.

### Follow up visits

Subjects will attend the IEMH at TASMC at the following intervals: screening Visit 1, Visit 2- Day 1- baseline day (allocation will be exposed at the end of baseline day; subjects allocated to SGLT-2 arm will meet the physician (RE) for instructions on the drug), Visit 3 Week 0- familiarization of protocol – meeting with the dietitian (AB) for V-Med arm only. Subjects allocated to the CRT arm will meet the physiologist (OK) or a physical instructor (AR) at their homes for familiarization. From familiarization day the 20-week count of the study period will start, and subjects will have an additional five “on site visits” at Week 1 (V-Med arm only; CRT – another visit at home after 1 week from beginning), Week 6 (V-Med arm only), Week 10 (all arms; CRT arm – end of study), Week 16 (V-Med arm only) and Week 20 (SGLTT-2 and V-Med arms) (Table 1).

**Table 1 Tab1:** Study flow chart

	Screening	Baseline day (W0–1)^e^	Familiarization of protocol^b^ (W0–2)	After 1 week (W1)	After 6 weeks (W6)	After 10 weeks^c^ (W10)	After 16 weeks (W16)	After 20 weeks (W20)
On site visit number	1	2	3	4	5	6	7	8
Informed consent	X							
Eligibility criteria form	X							
Medical discharge and list of drugs from primary physician + physical activity confirmation letter	X							
Blood examinations from last 3 months (for eligibility)	X							
Physical examination for vital signs by study physician	X					X		X
Screening blood and urine tests (biochemistry and endocrinology): a) Urine microalbumin, sodium, creatinine, free cortisol) b) TSH, FT4 c) 25 OH vitamin D	X							
Demographic details, questions on health status, lifestyle using MABAT questionnaire	X							
Functional and physical activity questionnaires	X							
Food frequency questionnaire	X							
Guidance about diabetes diary	X							
Drug guidance for drug arm only		X						
Dietary guidance for diet arm only			X	X	X		X	
CRT guidance for CRT arm only			X	X				
CRT guidance for drug and diet arms						X		
Height		X						
Body weight		X				X		X
Body circumferences		X				X		X
Body fat %, lean and muscle mass assessments using BIA method		X				X		X
Resting blood pressure		X				X		X
Resting energy expenditure		X				X		X
24 h blood pressure monitoring		X				X		X
Fasting plasma glucose and HbA1C		X				X		X
Testosterone (T) and bioavailable T		X				X		X
HOMA- Insulin X glucose/23.5		X				X		X
LH, FSH, Estradiol		X				X		X
Diabetes diary (self-monitoring glucose levels, change in drugs)		X				X		X
Functional and frailty tests	X					X		X
CRT diary (report on training days and performance)			X	X	X	X	X	X
Left of tablets count of drugs						X		X
Adherence to MedD	X					X		X
Food diary – 3 days			X			X		X
Quality of life	X					X		X
Phone calls (adverse events monitoring)			X	X	X	X	X	X
Encouragement using phone calls			X	X	X	X	X	X

^a^Allocation concealment until the end of baseline day – then allocation is introduced both to researcher and the subjects. Subjects allocated to SGLT-2 would meet physician at the end of the day for instruction of the use of the drug and will be supplied with drugs for 20 weeks). Subjects allocated to Diet and CRT groups will make an appointment for the following week (familiarization)

^b^For diet subjects – on site visit and for CRT subjects – familiarization at their homes

^c^At this week CRT group will finish the study and SGLTT-2 and V-Med add CRT on top of their current intervention. Familiarization of the CRT will be performed on the same week.

*Abbreviations*: *BIA* Bioelectrical Impedance Analysis, *BMI* Body Mass Index, *CRT* Circuit Resistance Training, *HbA1c* Hemoglobin A1C, *MedD* Mediterranean Diet

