#### Specific secondary aims

To profile community dwelling older people with T2DM in terms of overall health status, body composition, physical and metabolic function.To evaluate the effects of the three study arms on glycemic control, insulin resistance, hormonal and lipid profiles, blood pressure and energy expenditure in the community dwelling older subjects with T2DM.To assess the effects of the three study arms on sarcopenia and frailty measures in the community dwelling older subjects with T2DM.To evaluate whether or not there is a synergistic effect of either medical treatment with empagliflozin or the V-Med diet with the CRT intervention on weight reduction and functional status in community dwelling older subjects with T2DM. This will be done by comparing among each of the interventions alone, and with its combined effect with the other listed co-interventions.

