### Eligibility

#### Major inclusion criteria

Subjects who have T2DM in accordance with American Diabetes Association guidelines [33] and:
Are ≥65 years of age (inclusive) on the day of signing the informed consent form (ICF). Subjects may be treated with any anti hyperglycemic agent other than an SGLT-2 inhibitor.Perform ≤2 days a week of any leisure aerobic PA, who are able to walk independently either with or without an assistance device (cane or walker).HbA1C ≥6.5% to ≤8%.

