### Visit 1- screening

All potential eligible subjects will be invited for a screening Visit 1, during which the following information would be obtained:
Informed consent.Physician interview and physical examination.A questionnaire adapted from the national Israeli health and nutrition survey (MABAT) for the older people which includes demographic details, health status, lifestyle as well as descriptive details addressing the functional and physical state.A meeting with the research assistance (AL) (blinded during all study) to assess adherence to the Med-diet, using the PrediMed screener which was recently adopted to Israel.A meeting with the study’s physiologist (OK) comprised of a short interview and frailty and functional assessments.

Screening information from all subjects will be documented and kept in a screening log. Comparisons of baseline characteristics of the included vs. the excluded subjects will be performed at the end of the trial (age, gender, etc.).

### Visit 2- day 1

Subjects that were confirmed as eligible at the end of Visit 1 will be considered as “included subjects”. During Visit 2, subjects will be assigned a 5-digit number (their 5 first ID number’s digits) and the following information will be collected:
Following overnight fasting (12 h) patients will undergo: a) resting metabolic rate (RMR); b) Anthropometric assessment (then food is allowed); c) Fasting blood draw for routine glucose and hormonal profile; d) Blood Pressure (BP) (diastolic and systolic) and pulse measurements; e) eye examination.

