#### Blood tests

Hormonal profile of each subject will be obtained at each study period and will include: LH, FSH, estradiol (E2), bioavailable and free testosterone, insulin, IGF-1 and 25-hydroxy vitamin D. FPG and HbA1C levels will be obtained from HMO’s records (up to 3 months before the study and at week 10 and 20). For future examinations frozen plasma and blood samples from patients will be stored and kept at − 20 °C and − 80 °C respectively.

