##### Baseline comparisons

To test differences in continuous variables between the study groups the one-way analysis of variance (ANOVA) test will be performed (or Kruskal–Wallis one-way analysis of variance when normal distribution is rejected). For comparison of dichotomous or categorical variables the Chi square test will be performed.

The primary endpoints (% change in LBM and change in weight) will be analyzed using the analysis of covariance (ANCOVA) after 10 weeks and after 20 weeks (for diet and drug arms only) including several factors and covariates. Table 2 indicates the list of covariates and factors. Table 3 indicates the different outcomes and appropriate statistical method.

**Table 2 Tab2:** List of potential covariates and factors (partial list)

Factor or covariate	Type	Defined as
Treatment	Factor	SGLT2 inhibitor, diet, CRT
GLP1 agonists	Factor	Yes, no
Baseline body weight/ BMI	Covariate	–
HbA1c (%)	Covariate	–
Caloric consumption (Kcal)	Covariate	–
Resting metabolic rate (Kcal)	Covariate	–
Body fat %	Covariate	–
Strength (kg)	Covariate	–
Frailty or sarcopenia status	Factor	Frail or sarcopenic, pre-frail or pre sarcopenic and robust

*Abbreviations*: *BMI* Body Mass Index, *CRT* Circuit Resistance Training, *GLP-1* Glucagon-Like Peptide-1, *HbA1c* Hemoglobin A1C

**Table 3 Tab3:** The different outcomes and appropriate statistical method (partial list)

	Endpoint type	Statistical method
Primary outcome		
Change in body weight (%) from baseline to 10 weeks or to 20 weeks	Continuous	ANCOVA
Change in % lean body mass from baseline to 10 weeks or to 20 weeks	Continuous	ANCOVA
Proportion of participants having lost ≥2.5% at week 10 and 20	Binary	Logistic regression
Secondary outcomes		
Change in waist circumference from baseline to 10 weeks or to 20 weeks	Continuous	ANCOVA
Change in FPG and HB1Ac from baseline to 10 weeks or to 20 weeks	Continuous	ANCOVA
Change in sarcopenia and frailty status (improved vs. not improved; change from one level to the other) at week 10 and 20	Binary	Logistic regression
Change in strength and other functional abilities from baseline to 10 weeks or to 20 weeks	Continuous	ANCOVA
Change in systolic blood pressure from baseline to 10 weeks or to 20 weeks	Continuous	ANCOVA
Change in quality of life (improved vs. not improved; change from one level to the other) at week 10 and 20	Binary	Logistic regression

*Abbreviations*: *ANCOVA* Analysis of Covariance, *FPG* Fasting Plasma Glucose, *HbA1c* Hemoglobin A1C

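### Table 1 prints HOMA with divisor 23.5 and no units, where the index uses 22.5 (values 4.3% low), and insulin users, in whom HOMA does not index insulin resistance, are eligible

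*Protocol article*

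**What the plan says.** The protocol article's study flow chart (Table 1, under Follow up visits) has one row for the index: "HOMA- Insulin X glucose/23.5". It gives no units, and no other section gives a formula. The row is marked at the baseline day, week 10 and week 20. The same section and note c of the table say that the CRT arm finishes at week 10, so week-20 values exist only in the diet and drug arms.

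Insulin resistance is part of a secondary aim: "To evaluate the effects of the three study arms on glycemic control, insulin resistance, hormonal and lipid profiles" (Specific secondary aims). HOMA is the only measure of it in the article.

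On background treatment, the Major inclusion criteria state: "Subjects may be treated with any anti hyperglycemic agent other than an SGLT-2 inhibitor". Nothing in the Major exclusion criteria removes users of injected insulin. Under Blood tests, "Hormonal profile of each subject will be obtained at each study period", and that profile includes insulin, with no restriction by background therapy. Table 2 lists GLP-1 agonist use as a factor but not insulin use; its caption reads "List of potential covariates and factors (partial list"). Table 3, also marked partial, does not list HOMA.

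**The concern.** A named index has a fixed definition. If the analysts follow the printed one, each reported HOMA mean and absolute difference will be on a scale of its own. Readers who set the results beside other trials or a published threshold will be comparing unlike quantities. Missing units add to this, because the correct divisor depends on the glucose unit, and at least some glucose values come from outside the study: "FPG and HbA1C levels will be obtained from HMO’s records (up to 3 months before the study and at week 10 and 20").

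The second issue is one of validity. HOMA reads fasting insulin as the body's own response to fasting glucose. In a participant who injects insulin, the assay picks up the injected insulin to an extent that depends on the assay, so the product no longer indexes insulin resistance. It can also move when the dose is changed. If dose changes were more common in one arm, that arm's HOMA would shift without any change in insulin sensitivity. Unlike the divisor, this would not cancel between arms.

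**Working it through.** **Inputs.** From the article: divisor 23.5; three arms of 40; assessments at baseline, week 10 and (diet and drug arms) week 20. Not in the article: the normalisation of HOMA, which is the definition of the index (value 1 at insulin 5 µU/mL and glucose 4.5 mmol/L), and the factor 18 from mmol/L to mg/dL. Example values below are assumptions.

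**1. Can 23.5 be reproduced?**
- Glucose in mmol/L: 5 × 4.5 = 22.5.
- Glucose in mg/dL: 22.5 × 18 = 405.

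Neither gives 23.5. At the reference state the printed formula returns 22.5/23.5 = 0.957 instead of 1.

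**2. Size of the scale error.** Printed/correct = 22.5/23.5 = 0.9574, so values are 4.26% too low. Correcting them multiplies by 23.5/22.5 = 1.0444.

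| Insulin (µU/mL) | Glucose (mmol/L) | Product | /22.5 | /23.5 |
|---|---|---|---|---|
| 10 | 7.0 | 70.0 | 3.11 | 2.98 |
| 12 | 7.8 | 93.6 | 4.16 | 3.98 |
| 15 | 8.0 | 120.0 | 5.33 | 5.11 |

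**3. Effect on inference.** Write the printed value as k × H with k = 0.9574.
- Percent change: (kH₁ − kH₀)/(kH₀) = (H₁ − H₀)/H₀, so k cancels.
- ANCOVA on absolute change: the arm difference and its standard error are both multiplied by k, so the test statistic and p-value are unchanged.

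An ANCOVA on simulated data (three arms of 40, assumed distributions) agrees. One arm difference went from −0.560 with divisor 22.5 to −0.536 with 23.5, and its p-value was 0.090 under both. The p-values for percent change were also identical.

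**4. Units.** If glucose were entered in mg/dL and divided by 23.5, HOMA would be 405/23.5 = 17.2 times too high. An error of that size would probably be noticed, but stating the unit rules it out.

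**5. Insulin users.** HOMA is proportional to measured insulin. If measured insulin falls by a quarter after a dose reduction and glucose is unchanged, HOMA falls by 25% with no change in sensitivity. The share of insulin users is not given. Purely as an illustration, 10% to 25% of 40 is 4 to 10 participants per arm. If all of them in one arm had that fall and nobody else changed, the arm's mean percent change would shift by 0.10 × 25 = 2.5 to 0.25 × 25 = 6.25 percentage points. The article gives no figure for the share or for the fall, so this shows how the bias would scale and does not estimate it.

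**The case against.** The case for leaving this alone has several parts.

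- **The divisor is probably a one-digit slip.** It is the same constant in every arm and at every visit. No sample size, eligibility rule, primary endpoint or stated cut-off uses HOMA. This stands, and a reader who inferred that the comparison of arms on insulin resistance is wrong would be going too far: step 3 shows that it is not. What remains is a wrongly stated definition, which is a different matter from a detail left to another document.
- **The article does not say that insulin users enter the HOMA analysis.** One might infer from the unrestricted row in Table 1 and the hormone measurement in each subject that HOMA will be analysed in everyone. A visit schedule does not define an analysis set, however. The criteria are headed Major, Tables 2 and 3 are marked partial, and a restriction may sit in a full protocol or analysis plan that is not shown. This stands as a limit on the claim. The permission to enrol such participants is nevertheless explicit.
- **Nobody can say how large the insulin-user problem is.** True: neither the number of users nor the assay is given, and the article describes no insulin dose reduction in any arm. The HbA1c ceiling of 8% may keep the number low.
- **Changes in medication are recorded.** They are, in the diabetes diary. This makes the repair cheap but does not itself handle the changes in the analysis.

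A reader might also want to exclude anyone on insulin at any compared visit. That would select on treatment after randomisation, and if starting or stopping insulin differs by arm it would break the randomised comparison.

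**Conclusion.** The printed formula is wrong. Following it makes every HOMA value and absolute change 4.3% too low and not comparable with other studies or cut-offs, while percent changes and between-arm tests are unaffected. This rests only on the definition of the index and on glucose being in mmol/L.

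The eligibility text admits participants in whom HOMA is not a valid index, and the article states no way of handling them. This is the part that could alter a between-arm comparison, but its size is unknown, and the documents do not support calling the outcome meaningless or saying that all participants will be analysed this way. Nor do all participants have three values, since the CRT arm has none at week 20.

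The matter concerns one measure for a secondary aim. It merits correction because it costs almost nothing and HOMA is the only insulin-resistance measure in the article.

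**What to change.** 1. In Table 1, define HOMA as fasting insulin (µU/mL) × fasting glucose (mmol/L) / 22.5, with the units written out.
2. Make the main HOMA comparison in participants not using insulin at baseline: baseline to week 10 in all three arms, and to week 20 in the diet and drug arms. Baseline use precedes randomisation, so this restriction keeps the comparison randomised.
3. Add a sensitivity analysis for participants who start or change insulin later, identified from the drug list and diabetes diary already in Table 1.
4. Report per arm the numbers left out of the main HOMA comparison and the numbers who start or change insulin.

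The cost is one constant, one line of units, one analysis-set rule and a somewhat smaller n for HOMA. No new data are needed, and eligibility, treatment, primary endpoints and sample size stay as they are.

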### Main ascertainment of response variables

#### Anthropometric and sarcopenia

Anthropometric measurements will be obtained following a uniform protocol. Height, weight, waist and hip circumference will be measured twice. LBM, skeletal muscle mass (SMM), fat mass (FM) and % fat will be evaluated by the direct segmental multi-frequency bioelectrical impendence analysis (BIA) technique method using the ‘In-Body 770 body composition analyzer’. The In-Body 770 is a valid tool for the assessments of total body and segmental body composition [40]. Sarcopenia will be assessed in line with the consensus definition offered elsewhere [41] using three parameters: a) low skeletal muscle mass; b) low muscle strength; c) low physical performance [41]. Pre-sarcopenia will be defined as low skeletal muscle mass but normal strength and physical performance, whereas sarcopenia will be defined as having both low muscle mass with either low muscle strength or low physical performance. Severe sarcopenia will be determined by the presence of all 3 criteria (low muscle mass + strength + low performance). Skeletal muscle mass will be obtained by the In-Body (770) body composition analyzer. Shortly, the skeletal muscle index (SMI = skeletal muscle mass/body mass × 100) will be compared to gender-specific reference norms of young adults (aged 18–39 years). Sarcopenia will be defined as any value < 10.76 kg/m^2^ for men and < 6.76 kg/m^2^ for women [42]. Low muscle strength and low physical performance will be assessed using grip strength and gait speed test as described in the following paragraph on frailty.

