**Discussion:**

The combination and comparison of these diverse interventions to metabolic control may lead to better understanding of their mechanism of action with potential clinical implications in older individuals. Also, this study will provide evidence of the effectiveness of these interventions on delaying the progression from diabetes to sarcopenia and/or frailty.

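### The skeletal muscle index is computed as a percentage of body mass but judged against cut-offs in kg/m², and one label is defined in two ways, so sarcopenia status cannot be assigned as written.

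*Protocol article*

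**What the plan says.** All of the definitions stand in one paragraph of the protocol article, under Main ascertainment of response variables, Anthropometric and sarcopenia.

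- **Levels.** Three parameters are used: muscle mass, strength and performance. "Pre-sarcopenia will be defined as low skeletal muscle mass but normal strength and physical performance". By contrast, "sarcopenia will be defined as having both low muscle mass with either low muscle strength or low physical performance". Severe sarcopenia needs all three deficits.
- **Index.** "the skeletal muscle index (SMI = skeletal muscle mass/body mass × 100) will be compared to gender-specific reference norms" of young adults.
- **Cut-offs.** "Sarcopenia will be defined as any value < 10.76 kg/m^2^ for men and < 6.76 kg/m^2^ for women", with a literature citation.
- **Measurements.** "Height, weight, waist and hip circumference will be measured twice". Table 1 schedules height on the baseline day, and weight and bioimpedance at baseline, week 10 and week 20.

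The classification is used in two places. Table 3 lists as a secondary outcome, for logistic regression, "Change in sarcopenia and frailty status (improved vs. not improved; change from one level to the other) at week 10 and 20". Table 2 lists a single three-level factor that merges frailty and sarcopenia status; subgroup analyses may draw on the Table 2 factors.

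**The concern.** The formula has no height term, and the cut-offs carry a height-squared unit. No conversion is given, so a value from the formula cannot be placed above or below the cut-off. Pre-sarcopenia, sarcopenia and severe sarcopenia all start from low muscle mass, so all three levels depend on a criterion that is undefined as printed.

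The labels conflict as well. Someone with a low index and normal strength and performance is pre-sarcopenic under the three-level definition and sarcopenic under the cut-off sentence. If that person is not frail, the choice of sentence moves them between the middle and the worst level of the Table 2 factor.

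What is at stake is whether two analysts with the same data would obtain the same sarcopenia status. From this text they might not, and the gap between the readings is large.

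**Working it through.** The plan reports no computed figure on this point, so there is none to reproduce. The check is of units, then of what each reading would do.

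**Inputs from the protocol.** The formula and the cut-offs are as above. The Sample size section assumes body fat of 37, 36 and 40% in the three arms, with an SD of 6 percentage points. Lean mass is then 100 − 40 = 60% to 100 − 36 = 64% of weight.

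**Assumptions, not in the protocol.** Skeletal muscle is 40–60% of lean mass. BMI is 25–35 kg/m². The body fat figures are given by arm and not by sex, so the ranges cannot be refined for men and women separately.

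**Units.** Muscle mass (kg) / body mass (kg) × 100 is a percentage. The cut-offs are in kg/m². They differ in dimension.

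**Reading A: the percentage is compared with 10.76 and 6.76 as bare numbers.**

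- Index = lean % × muscle share of lean mass. Lowest: 60 × 0.40 = 24.0. Highest: 64 × 0.60 = 38.4.
- At a body fat of 40 + 3 × 6 = 58%, lean mass is 42% of weight and the index is still 42 × 0.40 = 16.8 to 42 × 0.60 = 25.2.
- To fall below 10.76, muscle would have to be under 10.76/64 = 16.8% to 10.76/60 = 17.9% of lean mass. For 6.76 the figures are 6.76/64 = 10.6% to 6.76/60 = 11.3%.
- In kilograms: 0.1076 × 80 = 8.6 kg of muscle for an 80 kg man, and 0.0676 × 80 = 5.4 kg for an 80 kg woman.

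Under these assumptions, practically nobody is classed as low.

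**Reading B: the index is muscle mass / height².** Since BMI = weight/height², the conversion is muscle mass/height² = (index %/100) × BMI. The cut-offs then correspond to these percentages of body mass:

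| BMI (kg/m²) | 10.76 kg/m² (men) | 6.76 kg/m² (women) |
|---|---|---|
| 25 | 43.0% | 27.0% |
| 28 | 38.4% | 24.1% |
| 30 | 35.9% | 22.5% |
| 35 | 30.7% | 19.3% |

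Set against an index of about 24–38%, the men's cut-off falls at the top of the range or above it at BMI 25 and 28, and inside it at BMI 30 and 35. Many men could be low. The women's cut-off falls inside the range at BMI 25, at its lower edge at BMI 28, and below it at BMI 30 and 35, so some women could be low.

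**One illustrative man** (assumed 28 kg muscle, 80 kg, 1.72 m): 28/80 × 100 = 35.0, far above 10.76 as a bare number. But 28/1.72² = 9.46 kg/m², which is below 10.76 kg/m². He is not low on reading A and low on reading B.

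**The case against.** The strongest reply is that the printed units show the intention. The cut-offs carry kg/m² and height is measured, so the formula may simply be a misprint for a height-squared index. On that reading the cut-offs separate people and the outcome works. This stands as far as it goes, and it rules out a stronger claim that a reader might infer: that no participant can be classed as low and the sarcopenia outcome is empty. That follows only if the printed units are ignored, and it also needs muscle-mass figures that the protocol does not give. The reply does not remove the contradiction. The text does not say which half is wrong, and the primary lean-mass outcome (Definition of main outcomes) is itself a share of weight, so a percentage index is not an obvious slip.

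Other inferences that the document does not support:

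- **That the Table 2 factor would be constant and no model could be fitted.** The factor merges frailty with sarcopenia, and the criteria in the Frailty section do not use the muscle index. It would still vary through frailty, and the frailty half of the Table 3 line is untouched.
- **That the index as printed favours the weight-loss arms.** If practically nobody can fall below the cut-off on the literal reading, a rise in the percentage after weight loss changes no classification.
- **That the coding as improved or not improved is part of the same fault.** The abstract does hope for evidence on "delaying the progression from diabetes to sarcopenia and/or frailty", but the secondary aim is only to assess effects on sarcopenia and frailty measures. A binary coding is a legitimate choice for a secondary outcome, and an ordinal model would be an analytic preference unrelated to this correction.

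It is also fair to say that the trial is described as exploratory, that the primary endpoints do not use this index, and that muscle mass and height are both collected, so nothing is lost beyond repair.

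**Conclusion.** Two contradictions hold. The index and its cut-offs are on different scales, and the cut-off sentence gives the name sarcopenia to a state that the same paragraph calls pre-sarcopenia. Neither depends on any assumption.

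The definition is best described as undetermined: low muscle mass runs from practically nobody on the literal reading to possibly many participants on the height-squared reading. That range does rest on the assumed muscle share of 40–60% and BMI of 25–35 kg/m², together with the protocol's own body fat figures.

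The reach is limited to the sarcopenia part of one secondary outcome and of one combined covariate or subgroup factor. This should be fixed before the analysis; it does not threaten the trial's main comparison.

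**What to change.** 1. State one index with cut-offs on the same scale. Skeletal muscle mass (kg) / height² (m²) matches the printed units and uses the height already taken at baseline. The protocol alone cannot show whether the formula or the units are in error, so check the choice against the cited source of the cut-offs. If a percentage index is what was meant, replace the cut-offs with percentage ones.
2. Reword the cut-off sentence so that a value below it defines low skeletal muscle mass. Do not delete it: it holds the only muscle-mass thresholds in the article.
3. Assign pre-sarcopenia, sarcopenia and severe sarcopenia solely by the three-criterion definition, and use that result in Tables 2 and 3.

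The cost is two reworded sentences, one look at the source and a line of code. No new measurement is needed. Settling it before the data are analysed by arm also keeps the choice of index from being influenced by the results.
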